# 5.2 Exclusion Criteria

Women who meet any of the following criteria (by self-report, unless otherwise specified, at screening, enrollment, or at anytime during participation, unless otherwise specified) will be excluded from this study:

- Are pregnant (based on a urine pregnancy test) or less than 6 months post-partum.
- Are currently breastfeeding.
- Are menopausal.
- Are currently using hormonal contraception or have used hormonal contraception in the previous 2 months.
- Are currently menstruating (at screening or enrollment visits – may be eligible for deferment).
- Have a positive HIV test at screening.
- Have a positive urine culture at screening (may be eligible for re-screening after treatment).
- Have a positive chlamydia, gonorrhea, or trichomonas result at screening.
- Have an abnormal Pap smear (if documentation of a negative result within the past year is not available).
- Have a clinically detectable genital abnormality (i.e., vulvar, vaginal, cervical and/or perianal ulcer and/or lesion or an abnormal wet mount).
- Have a history of Toxic Shock Syndrome, or a history of symptoms suggestive of Toxic Shock Syndrome.
- Have a history of intermenstrual bleeding in the 3 months prior to enrollment.
- Have had gynecological surgery or received treatment for syphilis, genital herpes, chlamydia, gonorrhea, trichomonas, or genital warts in the last 6 months.
- Have received treatment for candida, bacterial vaginosis, or urinary tract infection in the prior month.
- Have douched or used any vaginal products**,** including lubricants, feminine hygiene products, vaginal drying agents and sex toys during the 48 hours prior to enrollment.
- Have had sexual intercourse during the 48 hours prior to enrollment.
- Have evidence of acute or chronic hepatitis B infection (defined as + HBV core IgM, + HBV core IgG or + HBsAg).
- Have evidence of liver or kidney abnormalities (defined as ALT or AST >2x normal, Total bilirubin >1.2 mg/dl, and creatinine >1.2 mg/dl).
- Oral antibiotics in the past 7 days.

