6.4 Assessment of Participant Adherence with Study Product/Intervention(s)

The first application of investigational product will be done at the enrollment visit by the participant under the guidance of the study clinician. Participants will be instructed to apply the assigned investigational product once daily at bedtime for 13 subsequent days (see Appendix III).

Participants will be asked to record information on the number of times they administer study gel, time of each insertion, and emergence/resolution of specific symptoms in a study diary. Diaries will be reviewed at each visit.

Non-adherence will be defined as three or more days (out of 14) of missed product use. Participants who miss less than three days will (if practical according to their expected date of menses onset) be asked to apply product for additional days to attempt to achieve a full 14 days of product exposure. An additional participant will be recruited for each non-adherent participant. Participants who are non-adherent with the study protocol will be asked their reasons for non-adherence and this information will be recorded on the applicable study forms. Study procedures for Day 3, Day 7, Day 14, and the Final Visit will be re-scheduled as necessary. Participants will be instructed to call the study staff in the event of missed doses to re-schedule study visits.

Participants will be instructed to abstain from sexual relations throughout the course of the study. If a participant is found to have engaged in anal or vaginal sexual relations or experienced vaginal penetration with anything other than the study gel applicator throughout the study, this information will be recorded on applicable case report forms.

A participant with a clinical toxicity outcome (see Appendix IV) who is discontinued from further product use will be considered to have reached a study endpoint and will not be replaced. Standard clinical care will be provided and followed to resolution.

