**9.6 Criteria for Permanent Treatment Discontinuation for an Individual Participant**

The criteria for permanent treatment discontinuation of further study product/intervention(s) for an individual participant are:

- Treatment-related toxicity (see section 9), including pelvic inflammatory disease, deep epithelial disruption
- Requirement for prohibited concomitant medications such as oral antibiotics
- Pregnancy or breastfeeding
- Completion of treatment as defined in the protocol
- Request by participant to terminate treatment
- Clinical reasons believed life-threatening by the physician even if not addressed in the toxicity section of the protocol
- Unwillingness or inability to remain abstinent for the duration of the study.

The participant will continue to be followed with participant’s permission if study product/intervention (s) is discontinued.

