## 10.0 STATISTICAL CONSIDERATIONS

## 10.1 Overview and Statistical Designs Issues

## All subjects who receive treatment (1% tenofovir gel or matched placebo gel) will be included in all analyses. The primary objective of this study is to assess the mucosal response to repeated applications of 1% tenofovir gel or matched placebo gel by examining cervicovaginal secretions for cytokines chemokines, defensins, SLPI and lactoferrin as well as changes in the cell population in CVL pellets. A secondary objective is to assess whether the intrinsic antimicrobial (HSV, *E. coli* and *Staph aureus*) activity of CVL is altered following 14 days of daily intravaginal use of 1% tenofovir gel or matched placebo gel and correlate any observed changes in antimicrobial activity with changes in levels of mediators of mucosal immunity. An exploratory objective is to measure and compare the levels of tenofovir detected in serum and CVL.

The outcome is the level of individual proteins obtained after application of drug compared with placebo gel or total number of white blood cells and of specific cell types in CVL pellets. Differences between groups with respect to age and baseline amounts of mediators will be compared by *t* test. Differences between groups with respect to change in cytokines, chemokines, mediators of mucosal immunity, cell numbers, and antimicrobial activity will be compared by analysis of covariance and adjusted for baseline (after log transformation of data for cytokines, chemokines, and mucosal mediators). Differences between groups with respect to change in fold reduction in viral or bacterial infection after application of drug or placebo gel relative to titers in screening CVL samples will be determined by Wilcoxon nonparametric test (with exact p-values) on log transformed data. Calculations will be done using SAS software (version 9; SAS Institute).

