## Appendix IV: Outcomes, Diagnostics, and Follow-Up Procedures

Individual participants may withdraw from study participation at any time, for any reason, without loss of other benefits or services to which they may be entitled. Participants with any abnormal condition will be treated according to standard clinical practice.

| **Condition** | **Product Use** | **Evaluation** | | **Enrollment Action** | | **Follow-up and Treatment Action** | |
| --- | --- | --- | --- | --- | --- | --- | --- |
| Ulceration | Adverse clinical event, discontinue product use | Culture for genital herpes. |  | | Re-evaluate in 5 to 7 days. If the ulcer has become worse or not healed in 5 to 7 days, perform a biopsy. Ask the participant to return in 7 to 10 days for follow-up. | |  |
| Abrasion | Continue |  |  | | Re-evaluate by speculum examination in 48 to 72 hours. If the condition is worse, discontinue product use. If the condition is the same, continue product use. | |  |
| Generalized erythema or severe edema: A localized area of more than 30% of vulvar surface or combined vaginal and cervical surface affected by erythema | Adverse clinical event, discontinue product use |  |  | | Re-evaluate in 5 to 7 days. | |  |
| Vaginitis | Adverse clinical event, discontinue product use | Perform wet mount for *candida vaginitis, trichomoniasis,* and bacterial vaginosis. |  | | Manage with oral medication and re-evaluate in seven days. If resolved, restart product use. If the participant has asymptomatic candida vaginitis at the Day 7 visit she should continue product use and be re-evaluated at the Day 14 visit.[[1]](#footnote-2) | |  |

| Suspected cervicitis | Provisionally continue | Evaluate for *N. gonorrhoeae and C. trachomatis*. Perform wet mount for  *trichomoniasis.* | If laboratory results confirm pathogen, discontinue treatment. | Treat with oral medication and re-evaluate in 5 to 7 days. |
| --- | --- | --- | --- | --- |
| Petechial hemorrhage | Continue |  |  | Re-evaluate by speculum examination in 48 to 72 hours. If the condition is worse, discontinue product use. If the condition is the same, continue product use. |
| Ecchymosis | Continue |  |  | Re-evaluate by speculum examination in 48 to 72 hours. If the condition is worse, discontinue product use. If the condition is the same, continue product use. |

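### Section 5.2 extends three exclusion items to events on gel, contradicting the protocol's on-study rules and putting later lavage samples at risk

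*Protocol*

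**What the plan says.** The lead-in to Section 5.2 applies the exclusion criteria "at screening, enrollment, or at anytime during participation, unless otherwise specified) will be excluded from this study". Some items carry their own visit limit, for example "Have a positive chlamydia, gonorrhea, or trichomonas result at screening"; the HIV, urine culture and menstruation items are limited in the same way. Three items are not:

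- "Have a clinically detectable genital abnormality (i.e., vulvar, vaginal, cervical and/or perianal ulcer and/or lesion or an abnormal wet mount";
- treatment for candida, bacterial vaginosis or urinary tract infection within the past month;
- "Oral antibiotics in the past 7 days".

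Elsewhere the protocol treats the same events differently once a woman is on gel:

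- **Section 7.1 (Day 3, 7 and 14 visits):** staying in the study depends on how severe the abnormality is, as set out in Appendix IV.
- **Appendix IV:** gel continues for abrasion, petechiae, ecchymosis and asymptomatic candida at Day 7. For vaginitis, gel is stopped and then: "Manage with oral medication and re-evaluate in seven days. If resolved, restart product use".
- **Section 9.6:** permanent treatment discontinuation for "Requirement for prohibited concomitant medications such as oral antibiotics", with follow-up continuing if the woman agrees.
- **Section 9.7:** the list of reasons for leaving the study names none of these events.
- **Section 6.4:** a woman taken off gel for a clinical toxicity outcome "will be considered to have reached a study endpoint and will not be replaced". Section 13.5 also calls this a study endpoint.
- **Section 6.5:** all concomitant medications are allowed except vaginal products.
- **Section 10.1:** "All subjects who receive treatment (1% tenofovir gel or matched placebo gel) will be included in all analyses".

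**The concern.** Genital findings, inflammation and their treatment are closely tied to the mucosal response that the trial measures. Section 2.1 gives drug-induced inflammation and loss of host defences as the reason for doing the study. If such an event ends a woman's participation, whether her later samples exist depends on something that happened after randomisation and is related to the outcome. It may also happen more often in one arm.

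The trial has 12 women per arm, and Section 10.4 aims for complete retention because the sample is small. Whether site staff follow 5.2 or the visit instructions therefore matters. An analysis plan could not repair this, because the conflict decides who gives samples and not how they are analysed.

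**Working it through.** **1. The passages side by side**

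| Event on gel | Section 5.2, read literally | Other sections |
|---|---|---|
| Abrasion, petechiae, ecchymosis | Excluded, if counted as a genital lesion | Appendix IV: continue gel, re-examine |
| Asymptomatic candida at Day 7 | Excluded (abnormal wet mount) | Appendix IV: continue gel |
| Vaginitis treated orally, resolved | Excluded (abnormal wet mount, or treatment in the past month) | Appendix IV: restart gel |
| Oral antibiotics | Excluded (past 7 days) | 9.6: gel stopped for good, follow-up continues; 6.5: permitted |

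The first three rows set exclusion against continuing or restarting. The fourth sets exclusion against stopping gel with follow-up, and also sets 6.5 against 9.6. The Appendix IV restart conflicts with 9.6 only where the oral medication is an antibiotic; Appendix V distinguishes antibiotics from antifungals.

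**2. What would be lost**

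Post-dose lavage samples are due on Days 3, 7, 14 and 21, four in all. Assume that the sample at the visit where the event is found is still taken. Exclusion then costs:

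- found at Day 3: Days 7, 14 and 21, so 3 of 4;
- found at Day 7: 2 of 4;
- found at Day 14: 1 of 4.

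An event found at Day 3 or Day 7 costs the Day 14 sample, which marks the end of dosing.

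**3. The plan's own figure**

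Inputs from Section 10.2: SD about 0.5 log, difference about 0.55 log, two-sided 0.05, 80% power, 12 per arm.

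- n per arm = 2 × (1.960 + 0.842)² × 0.5² / 0.55² = 12.97, so 13. The stated 12 is reproduced to within one woman per arm.
- Power at 12 per arm: 76.9% (normal) or 73.1% (noncentral t).
- Detectable difference at 80% power: 2.802 × 0.5 × √(2/12) = 0.572 (normal) or 0.598 (t).
- With baseline adjustment, 80% is reached at an assumed baseline correlation of about 0.4.

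None of these figures depends on the 5.2 wording.

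**4. Illustration of lost samples**

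The number of women is assumed. The unadjusted t calculation uses noncentrality 0.55 / (0.5 × √(1/n₁ + 1/n₂)) and n₁ + n₂ − 2 degrees of freedom.

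| Women with a sample at a given visit | Power for 0.55 log | Detectable difference |
|---|---|---|
| 12 and 12 | 73.1% | 0.598 |
| 11 and 12 | 71.0% | 0.613 |
| 10 and 12 | 68.6% | 0.631 |
| 9 and 12 | 65.8% | 0.651 |
| 8 and 12 | 62.6% | 0.676 |
| 10 and 10 | 64.3% | 0.662 |

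This shows lost precision only. It says nothing about bias.

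**The case against.** The best defence is that the lead-in yields where the protocol specifies otherwise, and for lesions it largely does. The visit texts defer to Appendix IV. Sections 4.0 and 13.5 tie ineligibility for a genital abnormality to screening and enrollment. Section 9.7 lists no such event, and Section 5.0 sends withdrawal conditions to Section 13. Look-back windows of 7 days and one month are also typical of entry criteria. This stands in part: a careful reader can recover the intended rule for lesions. But 5.2 does not refer to Appendix IV, other items in the same list have limits written into them, and the disagreement between 6.5 and 9.6 remains on any reading.

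Four stronger readings are tempting, and the documents do not support them:

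- **Affected women are dropped from the analysis.** Section 10.1 includes all treated women, so only uncollected samples are at stake.
- **One event has several incompatible consequences throughout.** Being an endpoint, not being replaced, being followed and being analysed can all hold together. The conflict is between exclusion, continuing or restarting, and stopping with follow-up.
- **About 2 of 12 women per arm would be affected** (0.17 × 12 = 2.04, from the 17% rates of bruising and of erythema in Section 2.4). That earlier study used 0.3% and 1% gel once and twice daily and included HIV-infected and sexually active women. Counting bruising or erythema as a lesion is a further assumption.
- **The bias is toward no response.** Section 2.2 reports mainly lower mediators with tenofovir in vitro and with PRO 2000 in women, but inflammatory rises with nonoxynol-9. Losing inflamed women could hide a rise or exaggerate a fall.

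**Conclusion.** The contradiction is real and rests on the text alone. Read literally, Section 5.2 removes women from the study for events that Section 7.1, Appendix IV, 9.6 and 9.7 handle without removal. Separately, 6.5 and 9.6 disagree on oral antibiotics, and Appendix IV and 9.6 disagree on restarting gel after an antibiotic.

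If 5.2 were followed, up to three of four post-dose lavage samples per affected woman would go uncollected, for a reason related to the outcome and possibly unequally by arm. How many women, and in which direction any bias would run, cannot be derived from the documents; the power figures above illustrate assumed losses. The wording changes neither the stated sample size nor the analysis set. It should be corrected because the conflict governs sampling after randomisation in a 24-woman trial.

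**What to change.** - In 5.2, limit three items to the screening and enrollment visits as grounds for exclusion from the study: genital abnormality or abnormal wet mount, treatment in the past month, and oral antibiotics in the past 7 days.
- Do not delete the whole on-study phrase. It is the only on-study bar on hormonal contraception: 9.6 and 9.7 do not list it, 6.5 restricts only vaginal products, and Section 2.2 makes non-use part of the design. The sponsor should confirm the on-study reach of the remaining items, including pregnancy.
- State that women with on-study genital findings, treatment or a gel stop keep attending the scheduled lavage and safety visits with their permission, as 9.6 already provides after a gel stop, and are analysed in their randomised arm under 10.1.
- Reconcile 5.2, 6.5, 9.6 and Appendix IV on gel continuation and oral antibiotics. Which clinical rule applies is for the sponsor to decide.

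The cost is protocol wording, with no added visits, samples or participants.

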At the screening visit, eligible volunteers will come to the General Clinical Research Center (GCRC) at the Montefiore Medical Center (MMC)/Albert Einstein College of Medicine (AECOM). After informed consent is obtained, a medical, gynecological, and sexual history will be obtained. Urine will be collected for microscopy, culture, and a pregnancy test. If the pregnancy test is negative, a pelvic examination will be performed including a speculum exam with visual inspection, pH measurement, wet prep, and collection of a baseline cervicovaginal lavage (CVL) sample. CVL is a wash of the cervicovaginal area using 10 ml of phosphate buffered saline (PBS). A 10 ml syringe filled with PBS is aimed directly at the cervical os and posterior vaginal wall. The pooled fluid is aspirated and the entire volume collected. A Pap smear will be obtained if documentation of a negative result within the last year is not available. A cervical swab (DNA probe) for *N. gonorrhoeae* and *C. trachomatis* will be done. A bimanual exam will be performed for adnexal masses or tenderness. If there is evidence of a clinically detectable genital abnormality (i.e., ulcer, lesion or positive wet mount) or urinary tract infection, appropriate treatment and follow-up will be provided and the volunteer will be ineligible to continue in the study at this time. If a lesion or ulcer is present at this or any visit, a herpes culture will also be sent. Blood will be collected for a pregnancy test, HIV EIA, RPR, HSV serologies (type common and type-specific; Focus Technologies, Herpes Select), hepatitis B surface antigen, hepatitis B core immunoglobulin M (IgM) and hepatitis B core immunoglobulin G (IgG) (See Appendix I). Blood will also be collected for progesterone and estradiol levels to determine the phase of menstrual cycle (proliferative phase defined by serum progesterone  3 ng/ml) and to assess kidney and liver function. Subjects with no contraindications to study participation will be presumed eligible for enrollment.

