On the day of Enrollment (Day 0) (2-6 days after the next menses, within 30 days of screening), participants will return to the GCRC. Test results from screening will be reviewed. Urine will be collected for a repeat pregnancy test. If the pregnancy test remains negative, a speculum exam will be performed and the vagina and cervix will be visually inspected. A pH sample from the vaginal wall and a gentle swab for wet prep will be obtained. If there is evidence of a clinically detectable genital abnormality (i.e., ulcer, lesion or positive wet mount) appropriate treatment and follow-up will be provided and the participant will be ineligible to participate further at this time. If there is evidence of recent intercourse (sperm visualized on wet mount slide or positive PSA-specific membrane test), the participant will be ineligible to continue in the study. If there is evidence of acute or chronic hepatitis B infection or liver or kidney abnormalities, the participant will be ineligible to continue in the study. If the patient is eligible, a baseline CVL will be collected. Participants will be randomized in a double blind manner to receive the 1% tenofovir gel or matched placebo gel. The participant will insert one dose of study gel intravaginally under the guidance of the study clinician. Provided that the first dose is well tolerated, subsequent applications will be inserted once daily (preferably at bedtime) by the participants (see Appendix III) for 13 consecutive days. Subjects will be instructed and frequently reminded to apply each daily dose at bedtime. Study gels will be provided in single-use tubes with separate vaginal applicators and the participant will be provided with a study diary to record usage, symptoms and reasons for non-adherence.

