**Appendix I. Schedule of assessments**

|  | **Screening** | **Enrollment**  **(Day 0)** | **Day 3** | **Day 7** | **Day 14** | **Final Visit (Day 21)** |
| --- | --- | --- | --- | --- | --- | --- |
| Informed Consent | X |  |  |  |  |  |
| Sexual History | X | X*b* | X*b* | X*b* | X*b* | X*b* |
| Medical History/Concomitant Meds | X | X*b* | X*b* | X*b* | X*b* | X*b* |
| HIV EIA | X |  |  |  |  |  |
| Provide HIV/STI pre-test counseling | X |  |  |  |  |  |
| Provide HIV/STI test results and post-test counseling |  | X |  |  |  |  |
| Urine Microscopy/Culture | X |  |  |  |  |  |
| Urine pregnancy test | X | X |  |  |  |  |
| Serum pregnancy test | X |  |  |  |  |  |
| Pelvic Exam | X | X | X | X | X | X |
| Bimanual examination | X |  |  |  |  |  |
| Pap smear*c* | X |  |  |  |  |  |
| Vaginal pH | X | X | X | X | X | X |
| Wet Mount (*Trichomonas*, *Candida*, BV) | X | X | X | X | X | X |
| Inspection for sperm on wet mount and PSA | X | X | X | X | X | X |
| Herpes simplex virus culture | X*a* | X*a* | X*a* | X*a* | X*a* | X*a* |
| *N. gonorrhoeae/C. trachomatis* | X | X*a* | X*a* | X*a* | X*a* | X*a* |
| Progesterone and Estradiol | X | X |  | X | X |  |
| Serum tenofovir level |  | X | X | X | X | X |
| Liver function tests (ALT, AST, total bilirubin, hep B surface ant, hep B core IgM, hep B core IgG ) | X |  |  |  |  |  |
| Kidney function tests | X |  |  |  |  |  |
| *T. pallidum* (RPR) | X |  |  |  |  |  |
| Herpes simplex virus serology | X |  |  |  |  |  |
| CVL collection | X | X | X | X | X | X |
| Record Adverse Events |  | X | X | X | X | X |
| Distribute study supplies |  | X |  |  |  |  |
| Distribute Participant Diary |  | X |  |  |  |  |
| Review Participant Diary |  |  | X | X | X | X |
| Count used & unused supplies |  |  | X | X | X |  |

*a*If clinically indicated

*b*Interim history collected

*c*A Pap smear will be obtained if documentation of a negative result within the last year is not available

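### The liver and kidney exclusion in section 5.2 closes its list of limits with *and*; read literally this conflicts with its own stem, section 4.0 and Appendix II, so the text must say whether one abnormal value excludes

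*Protocol*

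**What the plan says.** - **Section 5.2, liver and kidney bullet:** the stem names an abnormality of the liver *or* the kidney, and the parenthesis that follows reads "defined as ALT or AST >2x normal, Total bilirubin >1.2 mg/dl, and creatinine >1.2 mg/dl". No other place in the protocol gives limits for these tests.
- **Section 5.2, lead-in:** exclusion applies to "Women who meet any of the following criteria". This governs how the bullets combine with each other. It does not say how several limits inside one bullet combine.
- **Section 5.2, hepatitis B bullet, directly above:** "defined as + HBV core IgM, + HBV core IgG or + HBsAg". It has the same format of a parenthetical definition, but the list closes with *or*.
- **Section 4.0, screening:** blood is drawn, among other reasons, "to assess kidney and liver function".
- **Section 4.0, Day 0:** the corresponding rule reads "evidence of acute or chronic hepatitis B infection or liver or kidney abnormalities, the participant will be ineligible to continue in the study". No limits are restated there.
- **Appendix II:** liver function tests (with the hepatitis serologies) and kidney function tests are separate rows, one to exclude liver disease and the other to exclude renal disease.
- **Appendix I:** the kidney row, "Kidney function tests | X", is marked at screening and at no later visit. The liver row is the same.

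**The concern.** An eligibility criterion is applied, and later monitored, as it is written; section 12.0 has the monitor check adherence to the protocol. The sentence that turns laboratory values into an eligibility decision can be read as needing a raised transaminase, a raised bilirubin and a raised creatinine all at once. On that reading a raised creatinine alone could never exclude anyone, and the kidney test could not do the job that Appendix II gives it.

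The same screening result could then be judged in two ways. A woman whose only abnormal value is creatinine above 1.2 mg/dl falls outside the literal definition in section 5.2, yet she has what the bullet's stem and section 4.0 would ordinarily call a kidney abnormality. Staff who enrol her and staff who turn her away could each cite the protocol. No scheduled test later in the study would bring the question up again.

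**Working it through.** The protocol states no figure on this point, so there is none to reproduce. The check is a truth table followed by a comparison of the sections.

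**1. Inputs (section 5.2).** Three yes/no flags:
- A: ALT or AST above twice normal
- B: total bilirubin above 1.2 mg/dl
- C: creatinine above 1.2 mg/dl

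**2. Patterns.** Three flags give 2 × 2 × 2 = 8 patterns. One has no abnormal value, so 8 − 1 = 7 have at least one.

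| Abnormal values | Patterns | Excluded if all three are required (A and B and C) | Excluded if any one suffices (A or B or C) |
|---|---|---|---|
| One only (A; B; C) | 3 | 0 | 3 |
| Two (AB; AC; BC) | 3 | 0 | 3 |
| All three (ABC) | 1 | 1 | 1 |
| Total | 7 | 1 | 7 |

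The literal reading leaves 7 − 1 = 6 of the 7 abnormal patterns unexcluded. The any-one reading leaves 7 − 7 = 0. These are counts of patterns, which are not equally likely. They show how far apart the two readings are and say nothing about how many women are affected.

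**3. Which reading the other text supports.**
- *Stem of the same bullet:* liver or kidney. If all three limits had to be exceeded together, no woman could qualify on liver alone or kidney alone, and the *or* would do no work. This supports any one.
- *Section 4.0, Day 0:* repeats liver or kidney. Supports any one.
- *Appendix II:* separate purposes for the liver and kidney tests. Supports any one.
- *Hepatitis B bullet:* closes with *or*. This cuts both ways. It shows what the authors wrote when one positive marker was meant to suffice, and it also lets a reader take the change to *and* in the next definition as deliberate.
- *Lead-in of section 5.2:* neutral, because it works between bullets.

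**4. Later checks.** Section 7.1 lists liver and kidney function at screening. The later study draws are:
- Day 0: progesterone, estradiol and tenofovir
- Day 3: tenofovir
- Day 7: progesterone, estradiol and tenofovir
- Day 14: progesterone, estradiol and tenofovir
- Final Visit: tenofovir

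Appendix I agrees. Scheduled liver or kidney function tests after screening: 0.

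**The case against.** The strongest reply is that the literal reading defeats its own sentence. A clinician would take the parenthesis as a list of what counts as an abnormality, with *and* merely closing the list. Section 4.0 gives no limits of its own, so it leans on section 5.2 and helps to interpret it. This stands in large part. It is why the point is an ambiguity whose literal reading conflicts with the surrounding text. It does not remove the point, because the operative definition still says something different from its stem when followed word for word.

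A reader might infer several stronger things that the document does not support:

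- *That a woman with one raised value will be enrolled.* This follows only if staff apply the literal reading against the stem and section 4.0.
- *That a given number of the 24 participants would be wrongly enrolled.* The protocol gives no frequency for any of these abnormalities, and the transaminase and bilirubin flags are unlikely to be independent. A count would rest on invented inputs.
- *That such a woman would receive tenofovir.* Allocation is 1:1 with placebo (section 4.0).
- *That this is the only laboratory safeguard.* Hepatitis B serology is a separate exclusion. The bullet is, however, the only numeric criterion on liver and kidney function.
- *That different sites would decide differently.* The study has a single site. Any disagreement would be between staff, or between staff and the monitor.
- *That nothing at all could detect a problem later.* Only scheduled tests are absent. Section 7.2 provides for clinical assessment of reported adverse events, and section 13.5 lets the investigator withdraw a participant for safety.

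The stakes should also be kept in proportion. Section 2.3 reports limited but detectable absorption in the earlier Phase I study of the gel, with a median Cmax of 3.4 ng/ml (approximately 1% of the oral steady-state maximum) and no clinically significant systemic toxicity. Dosing here lasts 14 days.

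**Conclusion.** The point holds as a drafting fault in an operative safety criterion. Followed word for word, section 5.2 excludes 1 of the 7 abnormal patterns, while the any-one reading suggested by the stem, section 4.0 and Appendix II excludes all 7. The conflict can be seen on the page and needs no assumption about prevalence. Its practical effect depends on how staff read the sentence, which the document cannot settle, so no number of affected women is claimed.

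No endpoint, analysis or sample-size figure is touched. The fault is still worth correcting before enrolment, because it bears on who may be randomised and no scheduled test would revisit the decision. Whether the limits themselves are clinically suitable is not judged here.

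**What to change.** Reconcile the bullet in section 5.2 with its own stem, with section 4.0 and with Appendix II, so that the text states outright whether one value beyond its limit is enough to exclude. Those places point to a definition that opens with *any of* and closes with *or*, as the hepatitis B definition already does. The three limits stay as they are. If the sponsor does mean that all must be exceeded together, the stem, section 4.0 and the purposes in Appendix II have to be changed to agree.

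The cost is a few words of amendment. With the any-one wording there would be slightly more screen failures than the literal reading would give. If staff already treat the limits as separate, nothing changes in practice.
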